### Sample size determination

The sample size was determined by assuming that the mean of the VAS measures will be 5 ± 1 in the control group and 3 ± 1 in the intervention group. A sample size of 25 subjects per group will allow for a difference of at least 1 point between the two groups, with a power of 93.5% and a type I error of 5%. An additional 20% of subjects are added to take into account possible loss of follow-up, bringing the total to 30 subjects per group. Patients can withdraw from the study at any time, for any reason, and their decision to stop their participation will not affect their regular standard of care. Withdrawn participants will not be replaced. Patients that withdraw from the study will be considered as being lost to follow-up. There is no anticipated harm and compensation for trial participation. Moreover, there will be no provision for post-trial care. The patient will return to the usual standard of care pathway if needed.

A recruitment of 6–8 participants per month is necessary to achieve the required sample size. Given that the Department of Neurosurgery treat 3–5 patients per week for disc herniation surgery, sufficient recruitment should be feasible in the pre-defined timeframe. Moreover, the principal investigator will coordinate the follow-up and end-of-study visit with those scheduled with the surgeon to avoid loss of data.

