## Abstract

**Background:**

The prevalence of post-surgical lumbar neuropathic radiculopathy is approximately 30%. Poor response to the recommended treatments for neuropathic pain, namely antidepressants and/or gabapentinoids, requires the development of new techniques to prevent chronic pain. One such well-tolerated technique is the administration of autologous plasma enriched in platelets and fibrin (PRF). This approach is largely used in regenerative medicine owing to the anti-inflammatory and analgesic properties of PRF. It could also be an interesting adjuvant to surgery, as it reduces neurogenic inflammation and promotes nerve recovery, thereby reducing the incidence of residual postoperative chronic pain. The aim of the present study is to evaluate the benefit of periradicular intraoperative application of PRF on the residual postsurgical neuropathic pain after disc herniation surgery.

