## Background

Neuropathic pain is defined by the International Association for the Study of Pain (IASP) as “pain resulting from an injury or disease affecting the somatosensory system” [1]. From an epidemiological point of view, several large surveys using screening tools have been carried out in different countries. The STOPNEP study carried out in France on more than 30,000 individuals made it possible to estimate the prevalence of chronic pain at approximately 30%, including 7% with neuropathic characteristics, and similar results were yielded in a French 2018 study by Chenaf et al. [2, 3]. In other countries, similar estimates of prevalence (i.e., 6–10%) have been reported [4]. Among the most cited causes is a disc herniation, in almost 1 out of 5 cases [5]. Neuropathic pain remains underdiagnosed in general, with a significant delay in treatment, leading to excessive consumption of opiates and medical nomadism [6]. Thus, the intensity, persistence and impact of chronic pain significantly affect quality of life [7].

Acute lower back pain is one of the most commonly observed acute pains in clinical practice. Its natural history is most often favorable, with healing usually occurring within a few weeks. The problem appears when nerve root pain occurring in the lower back as a result of discoradicular conflict persists. Among these patients, some will benefit from spinal surgery. However, after spinal surgery, some patients will develop residual chronic pain, which has been shown to occur in 10–50% of cases [8]. For approximately 50–70% of these cases, we note the persistence of neuropathic symptomatology [9].

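### The planning values of 5 ± 1 versus 3 ± 1 do not fit a population in which about 30% are expected to have residual neuropathic pain, so the 93.5% power holds only if the SD is 1

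*Protocol article*

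**What the plan says.** Protocol article, Sample size determination, for controls: "The sample size was determined by assuming that the mean of the VAS measures will be 5", the spread there being given as ± 1. The value for the PRF arm is "3 ± 1 in the intervention group". On precision the section says: "A sample size of 25 subjects per group will allow for a difference of at least 1 point between the two groups". The power claimed for that difference is 93.5%, at a type I error of 5%. The only allowance made is 20% for loss to follow-up, giving 30 per group.

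Two other places say how common residual neuropathic pain is:

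- Abstract, Background: "The prevalence of post-surgical lumbar neuropathic radiculopathy is approximately 30" per cent.
- Background, on residual chronic pain after spinal surgery: "which has been shown to occur in 10–50% of cases". For roughly 50–70% of those cases, "we note the persistence of neuropathic symptomatology".

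Three further places fix who contributes to the comparison. The inclusion criteria (Setting and patient recruitment) admit adults with radiculopathy from a lumbar disc herniation who are scheduled for surgery. Nothing there predicts or requires residual pain. The Statistical analysis section defines the ITT set as all consenting randomised patients and plans no subgroup analyses. Outcomes makes the primary measure a leg-pain VAS from 0 to 10 at 6 months, with the neuropathic nature of the pain confirmed by examination and a DN4 score of at least 4.

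**The concern.** The trial aims to prevent residual neuropathic pain, and on the article's own figures most operated patients will not have it. Yet the planning values treat each arm as one homogeneous group centred on moderate pain with little spread. A normal distribution with mean 5 and SD 1 puts about 98% of controls above a VAS of 3.

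If the values really describe only patients with residual pain, the comparison over everyone randomised has a smaller mean difference and, in the control arm at least, a larger SD than planned. The power claimed for the primary comparison would then not be the power the design has. Readers judging an inconclusive result would be working from the wrong figure.

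**Working it through.** **Inputs from the article.** Means 5 and 3, SD 1 in each arm; 25 analysed per group; type I error 5% (taken as two-sided); stated power 93.5% for 1 point; share with residual neuropathic pain about 30%. The Background figures give 0.10 × 0.50 = 5% to 0.50 × 0.70 = 35%.

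**Input that the article does not give.** The 6-month VAS of patients without residual neuropathic pain. It is assumed below and varied.

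**1. The plan's own figure.** For a two-sample t-test the noncentrality is d·√(n/2) = 1 × √12.5 = 3.54 on 48 degrees of freedom. Power is 93.4% (94.2% by the normal approximation), so the stated 93.5% reproduces. It belongs to a 1-point difference with SD 1. The assumed 2-point difference would give more than 99.99%.

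**2. Can mean 5 and SD 1 hold for all controls?** Let a share p be affected and let g be the gap in mean VAS between affected and unaffected patients. The total variance is at least p(1 − p)g², even with no spread inside either group.

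- With SD 1 and p = 0.30: g ≤ 1/√(0.30 × 0.70) = 1/√0.21 = 2.18. The unaffected mean is 5 − p·g ≥ 5 − 0.30 × 2.18 = 4.35.
- Using the article's highest figure for any residual chronic pain, p = 0.50: g ≤ 1/√0.25 = 2.0, and the unaffected mean is at least 5 − 0.50 × 2.0 = 4.0.

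This bound needs no assumed VAS. Patients counted as free of residual neuropathic pain, or even of any residual chronic pain, would have to average 4 or more out of 10.

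**3. Illustrative power over all randomised patients.** Each arm is a mixture with

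mean = p·m + (1 − p)·m₀

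variance = p(s² + m²) + (1 − p)(s₀² + m₀²) − mean².

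Take p = 0.30, with affected patients at 5 (SD 1) in controls and 3 (SD 1) under PRF. With unaffected patients at 0 (SD 0):

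- Control: mean 0.3 × 5 = 1.5; variance 0.3 × 26 − 2.25 = 5.55; SD 2.36.
- PRF: mean 0.3 × 3 = 0.9; variance 0.3 × 10 − 0.81 = 2.19; SD 1.48.
- Difference 0.6; pooled SD √((5.55 + 2.19)/2) = 1.97.

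The same steps for the other assumed values, by noncentral t with 25 per group:

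| Assumed VAS, unaffected | Control mean (SD) | PRF mean (SD) | Power |
|---|---|---|---|
| 0 (SD 0) | 1.5 (2.36) | 0.9 (1.48) | 18% |
| 1 (SD 1) | 2.2 (2.09) | 1.6 (1.36) | 22% |
| 2 (SD 1) | 2.9 (1.70) | 2.3 (1.10) | 31% |
| 3 (SD 1) | 3.6 (1.36) | 3.0 (1.00) | 41% |

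The mixtures are not normal. Simulated t-tests for the first two rows gave 16% and 20%. At p = 0.35 the four values run from 22% to 52%.

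**4. If only DN4-positive patients were scored.** 0.30 × 25 = 7.5, so 7 or 8 per group. With SD 1, power is 41–46% for 1 point and 93–96% for 2 points.

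**The case against.** The strongest replies, and what stands of each:

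- **The power calculation is right.** It is. A reader might infer an arithmetic error, but the 93.5% follows from its inputs. The problem lies in the inputs.
- **The outcome is leg pain in everyone, so patients who are not DN4-positive may still score above 0.** True, and the article gives no VAS for them. A reader might take 18% as the trial's real power; that figure rests on the extreme assumption that all unaffected patients score 0. Nor does the SD more than double in general: in the table that happens only in the control arm when unaffected patients are put at 0 or 1. The bound in step 2 uses none of these assumed values.
- **The prevalence figures are loose.** The 10–50% concerns spinal surgery in general, and the 30% carries no time point. They are still the only frequencies the article offers, and the conflict remains even at 50% with any chronic pain.
- **The values may describe DN4-positive patients only.** The Outcomes section leaves that reading open. It gives 93–96% for the assumed 2-point effect, so a reader should not conclude that power collapses under every reading. But 93.5% is attached to 1 point, for which this subset gives 41–46%. The subset is also formed after randomisation, and it is not the stated ITT set.
- **A larger effect would rescue the design.** If PRF abolished all residual pain at 30% prevalence, power would be about 88% with the others at 0 and 72% with the others at 1. At 35% with the others at 0 it would be about 94%. The planning values assume a mean of 3 under PRF, not abolition.
- **The analysis is Bayesian and may use a generalized model.** The t-test figures therefore only approximate the planned analysis, as does the plan's own 93.5%.

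**Conclusion.** The planning inputs conflict with the article's own expectation of about 30% (5–35%) residual neuropathic pain in an unselected surgical population analysed as randomised. The firm part is the bound: a mean of 5 with SD 1 over all controls forces the unaffected 70% to average at least 4.35 out of 10. The 93.5% is valid only as power for a one-SD difference, which is 1 point only when the SD is 1.

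The 18–41% range is illustrative. It assumes 30% affected, a fall from 5 to 3 in those patients, and a VAS of 0 to 3 in the rest. The documents do not support presenting any single value as the true power.

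A reader might also apply an SD near 2.4 to both arms and infer a detectable difference of 1.9 to 2.4 points. That should not be used: the SD comes from a mixture whose control mean is 1.5, and PRF cannot lower a mean by more than its own size.

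**What to change.** Keep the 60 patients and rewrite the planning paragraph:

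1. State which population the 5 ± 1 and 3 ± 1 describe (all randomised patients, or those with confirmed residual neuropathic pain), and give their source.
2. For all randomised patients, derive the mean and SD of each arm from the expected share with residual pain (about 30%, range 5–35%) and an explicitly assumed VAS, with a range, for the rest.
3. Replace the unconditional power statement with wording such as: *25 evaluable patients per group give about 93% power at a two-sided 5% level for a difference of one SD, which is 1 point only if the SD is 1; under the assumptions listed for all randomised patients, power ranges from … to ….*

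Nothing need be added on interval reporting, because the Statistical analysis section already plans 95% credibility intervals. The cost is a rewritten paragraph and a less favourable stated power, with no extra patients.

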### Statistical analysis

The analyses will be carried out using Bayesian methods.

Firstly, a descriptive analysis will be carried out. For the categorical variables, the frequency of each value and the cumulative frequency will be given. For the quantitative variables, location parameters (mean, median, minimum, maximum, first and third quartiles) and dispersion parameters (standard deviation, variance, range and interquartile range) will be given. The parameters will be estimated firstly on raw data, and secondly within the Bayesian paradigm, on the posterior distribution, for each variable.

Secondly, to compare the difference of the means of the VAS, a Bayesian linear regression will be performed. The regression will be simple linear or generalized depending on the distribution of the data. To meet the secondary objectives, Bayesian linear regressions will be performed for continuous variables, and Bayesian logistic regressions for categorical variables.

The regressions will be firstly carried out without adjustment and secondly with an adjustment on sex and age. Subgroup analyses are not planned.

The priors will be on the one hand very uninformative and on the other hand informative in the context of a sensitivity analysis.

For each analysis, the posterior distribution of the parameter of interest (rate, proportion, mean, odds ratio, regression coefficient, etc.) will be estimated using Markov chain Monte Carlo (MCMC) draws. The default number of iteration is 200,000 with a burning of 10,000 and a thinning of 2. Algorithm convergence will be assessed graphically and with the Gelman and Rubin’s convergence diagnostic. Autocorrelation will be assessed graphically and, if required, the number of iterations and thinning will be increased to reduce as much as possible the autocorrelation.

Credibility intervals will be calculated at 95% using the quantile method. A particular factor will be considered to exert an effect on the variable in question if the probability that the effect is greater than the reference value is greater than 0.975 or less than 0.025.

The proportion of missing data will be given for each variable. Missing data will be treated by simple deletion of cases if these values are very few or by multiple imputation in the opposite case.

Two different data sets will be defined:The intention-to-treat (ITT) data set, which contains all subjects who give their consent for the study and who undergo randomization, whether they follow or not the protocol properly (for instance if they do not follow the treatment or the visits planning).The per-protocol (PP) data set, which contains all subjects who, after randomization, undergo the treatment and who follow the protocol as planned.

The datasets analyzed during the current study and statistical code are available from the corresponding author on reasonable request, as is the full protocol.

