**Methods:**

A randomized, prospective, interventional, controlled, single-blind study with evaluation by a blind outcome assessor will be performed in Strasbourg University Hospital. We will compare a control group undergoing conventional surgery to an experimental group undergoing surgery and periradicular administration of PRF (30 patients in each arm). The primary outcome is the intensity of postoperative neuropathic radicular pain, measured by a visual analog scale (VAS) at 6 months post-surgery. The secondary outcomes are the characteristics of neuropathic pain (NPSI), the quality of life (SF-12 and PGIC), the presence of anxiety/depression symptoms (HAD), and the consumption of analgesics. We will also carry out transcriptomic analysis of a panel of pro- and anti-inflammatory cytokines in blood samples, before surgery and at 6 months follow-up. These gene expression results will be correlated with clinical data, in particular, with the apparition of postoperative neuropathic pain.

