### Outcomes

Study outcomes are assessed by a designated, blinded study investigator, and the patient (self-assessment), who is also blind to their treatment arm. All outcomes will be assessed at baseline (preoperatively) and at 2 weeks and 6 months after the surgery.

The primary outcome is the intensity of postoperative neuropathic radicular pain, measured by a visual analog scale (VAS). The neuropathic radicular pain will be confirmed by a clinical examination and a “Douleur Neuropathique 4” (DN4) score ≥ 4. Thus, VAS for leg pain will be measured during all follow-up visits: baseline (preoperative), 2 weeks and 6 months postoperative. VAS leg pain will be scored on a 0 to 10 points scale with increments of 1 point (0 being zero pain and 10 being the maximum pain possible).

In order to assess the presence and the neuropathic pain characteristics, the quality of life and the anxiety/depression syndromes, secondary outcomes will be measured at baseline (preoperative), 2 weeks and 6 months postoperative:The incidence and characteristics of residual neuropathic pain, measured by the DN4 and the Neuropathic Pain Symptom Inventory (NPSI) questionnaires, respectively;The evolution of quality of life with the 12-item Short Form Survey (SF-12) and Patients’ Global Impression of Change (PGIC) questionnaires;Anxiety and depressive symptoms with the Hospital Anxiety and Depression (HAD) questionnaire;The level of gene expression of a panel of pro- and anti-inflammatory cytokines in the blood (Table 1) using multiplex quantitative PCR;The use of analgesics;Incidence of adverse events (AE) and serious adverse events (SAE).

**Table 1 Tab1:** Panel of genes used for gene expression analysis

**Pro-inflammatory cytokines**	TNF-α, IL-1β, IL-6, IL-8, IL-17, IL-18, MCP-1, RANTES, CXCL2, fractalkine
**Anti-inflammatory cytokines**	IL-2, IL-4, IL-10, IL-1RA
**Signal transduction proteins**	IκB, NFκB p65 subunit

*TNF* tumor necrosis factor, *IL* interleukin, *MCP* monocyte chemoattractant protein, *RANTES* regulated on activation normal T cell expressed and secreted, *CXCL2* chemokine (C-X-C motif) ligand 2, *IL-1RA* interleukin 1 receptor antagonist, *NFκB* nuclear factor kappa B, *IκB* inhibitor of nuclear factor kappa B

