### Timeline and description of processes

An initial selection of patients will be carried out during a routine consultation with the practicing neurosurgeon, 30 days (± 20 days) prior to surgery. During this visit, the patient will be provided with the necessary study information, the eligibility criteria will be verified, and a clinical examination will be carried out. If the patient is eligible and decides to participate, an enrolment visit will be carried out 1 week (± 6 days) prior to surgery. At this visit, which takes place at the pain center (Strasbourg University Hospital), written informed consent is provided obtained from the participant, who will then complete baseline questionnaires and undergo a clinical examination. Randomization is also carried out at this visit, by using web-based randomization software (CleanWEB® clinical trial management platform). The details of randomization will remain unavailable to the medical examinator and the participant during the study. Randomization will be carried out using an allocation ratio of 1:1, which will determine the treatment arm of the patient: the interventional group (surgery and PRF application) or the control group (surgery alone). The allocation sequence is generated by the statistician of the study, using computer-generated random numbers. There will be no special criteria for discontinuing or modifying allocated interventions. To reduce predictability of a random sequence, the randomization will be carried out with two randomly distributed block sizes. Randomization will be carried out without factors of stratification. A specified investigator will carry out the enrolment visits and randomization process. This investigator and the surgeons carrying out the intervention will be the only investigators not blind to participants’ treatment arm. Blinding of the evaluating investigators will remain in place until statistical analysis of the study results has been finalized. Equally, participants are blinded to the intervention that they have received (experimental or control).

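### The VAS regression omits the preoperative leg-pain VAS that every patient already provides; adding it is a nearly free gain in precision

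*Protocol article*

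**What the plan says.** The primary outcome is leg-pain intensity "measured by a visual analog scale (VAS) at 6 months post-surgery" (Abstract, Methods). In the Statistical analysis section, "to compare the difference of the means of the VAS, a Bayesian linear regression will be performed", and the covariates are then named: "The regressions will be firstly carried out without adjustment and secondly with an adjustment on sex and age". The form of the model is left open: "The regression will be simple linear or generalized depending on the distribution of the data". No baseline score is listed as a covariate, and no change-from-baseline analysis is described anywhere in the article.

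The baseline value exists. Under Outcomes, "VAS for leg pain will be measured during all follow-up visits: baseline (preoperative), 2 weeks and 6 months postoperative", scored 0 to 10 in whole points each time. The section describing the clinical examination and questionnaires adds that DN4, NPSI, HAD and SF-12 are also completed before surgery; only the PGIC is restricted to the postoperative visits.

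Baseline pain is not balanced by design either: "Randomization will be carried out without factors of stratification" (Timeline and description of processes).

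**The concern.** In a two-arm trial with a continuous outcome measured on the same scale before and after treatment, the preoperative score is the obvious covariate. It can absorb part of the between-patient variation in the 6-month score, and it corrects for a chance difference between arms in starting pain. Here neither the model nor the randomisation uses it, although the planned number of evaluable patients is only 25 per arm.

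At stake is the width of the credible interval for the main result and how far a baseline difference in pain can shift the estimate. The article states the covariate set positively, so this is not a detail left to a plan we cannot see. A later analysis plan would either follow that sentence and omit baseline VAS, or depart from it.

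**Working it through.** **Inputs from the Protocol article (Sample size determination, Statistical analysis)**
- 25 evaluable patients per arm, 30 randomised per arm
- Difference 1 point: "A sample size of 25 subjects per group will allow for a difference of at least 1 point between the two groups"
- SD 1 in each arm: "mean of the VAS measures will be 5 ± 1 in the control group and 3 ± 1 in the intervention group"
- Stated power 93.5%, type I error 5%
- Decision rule at posterior probability 0.975 or 0.025, which with a vague prior corresponds to a two-sided 5% test

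**Assumption.** The correlation r between preoperative and 6-month leg VAS is not in the article. I take r = 0.1 to 0.6.

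**Step 1: reproduce the plan's figure.** The standard error of the difference is SD × √(2/n) = 1 × √(2/25) = 0.283. With a 1-point difference, the two-sided noncentral t-test gives 93.4% and the normal approximation 94.2%. The stated 93.5% is therefore the power of an unadjusted comparison at 1 point and SD 1. (The means of 5 and 3 imply 2 points, at which power exceeds 99.99%. That mismatch is a separate matter.)

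**Step 2: add baseline VAS.** Residual SD = SD × √(1 − r²); equivalent number per arm = 25/(1 − r²); one further degree of freedom is used.

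| r (assumed) | Variance reduction (r²) | Residual SD | SE | Equivalent n per arm | Power, 1 point |
|---|---|---|---|---|---|
| none | – | 1.000 | 0.283 | 25.0 | 93.4% |
| 0.1 | 1% | 0.995 | 0.281 | 25.3 | 93.6% |
| 0.2 | 4% | 0.980 | 0.277 | 26.0 | 94.2% |
| 0.3 | 9% | 0.954 | 0.270 | 27.5 | 95.3% |
| 0.5 | 25% | 0.866 | 0.245 | 33.3 | 97.9% |
| 0.6 | 36% | 0.800 | 0.226 | 39.1 | 99.1% |

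These figures leave out the small extra variance from estimating the slope. For a normally distributed covariate this averages a factor of 1 + 1/(50 − 4) = 1.022. At r = 0.1 that gives 0.99 × 1.022 = 1.012, so the bottom row of the range should be read as no gain. At r = 0.3 it gives 0.91 × 1.022 = 0.930, still a reduction of about 7%.

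**Step 3: if the SD is larger than planned.** With an assumed SD of 2 and a 1-point difference, power is 41% unadjusted. With baseline VAS it is 41% at r = 0.1, 44% at 0.3, 52% at 0.5 and 58% at 0.6.

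**Step 4: chance imbalance.** The difference in mean baseline VAS between arms has standard error √(2/25) = 0.283 baseline SDs. An imbalance of that size moves the unadjusted estimate by slope × imbalance. With equal SDs at the two times the slope equals r, so the shift is 0.1 × 0.283 = 0.03 SD, 0.3 × 0.283 = 0.08 SD, or 0.6 × 0.283 = 0.17 SD. At SD 1 these are 0.03, 0.08 and 0.17 points on the 0 to 10 scale.

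**The case against.** The strongest reply is that nothing here is an error. Randomisation makes the unadjusted estimate unbiased, and its interval already allows for chance baseline differences. On the plan's own inputs power is 93.4% without any covariate, so there is little to gain. The baseline score is taken before the herniation is removed and the outcome is residual pain 6 months later, so a low correlation cannot be ruled out from the text. All of this stands. It limits the point to efficiency and makes the size of the gain conditional on r.

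Several stronger readings are tempting, but the article does not support them.
- **That baseline imbalance passes in full into the result.** It does not; it is scaled by the slope, as in Step 4.
- **That the gain in power is large at the planned design.** Large gains appear only for standardised effects well below the planned 1 SD. Such effects are not in the article and have to be labelled as assumptions, as the SD of 2 is here.
- **That running unadjusted and adjusted models, on both the intention-to-treat and per-protocol sets, with a model form chosen from the data, inflates the type I error.** This is a different question from the missing covariate. It presumes that any positive analysis may be claimed. The article does give an order, unadjusted first, and its sample size matches an unadjusted comparison. Naming the deciding analysis is commonly left to the analysis plan.
- **That the DN4 logistic model should also be adjusted for its baseline at no cost.** With the abstract's prevalence of about 30%, 50 patients give about 15 events. Treatment, sex, age and baseline DN4 would make four coefficients, under four events each. Adjustment also changes the odds ratio being estimated, from marginal to conditional.

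**Conclusion.** The point holds as a nearly free improvement, not as a flaw in validity. The article names its covariates and leaves out the preoperative value of the primary outcome, which it already collects and does not balance by stratification.

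The size rests entirely on the assumed correlation. Over r = 0.1 to 0.6 it runs from negligible to the equivalent of 56% more patients. At the planned effect and SD the gain in power is modest because power is already high, and the benefit is mainly a narrower credible interval. It becomes material if the 6-month SD turns out larger than 1. I am confident that the covariate is missing and that including it is sound; I am not confident about how much it will yield.

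**What to change.** In the Statistical analysis section, name as the primary model the Bayesian linear regression of 6-month leg VAS on treatment group, adjusted for preoperative leg VAS, sex and age. Keep the unadjusted regression as a supportive analysis. For the continuous secondary scores (NPSI, SF-12, HAD), add the score's own preoperative value to its model. Leave the DN4 logistic model out of this change.

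The cost is a sentence or two of text and one parameter per model. No new data, visits or patients are needed. The change should be made before the data are unblinded.

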During the immediate postoperative period, all analgesics are permitted as per standard of care: paracetamol, NSAIDs, nefopam, tramadol, lidocaine, ketamine, morphine. For residual postoperative pain, level 1, 2, or 3 analgesics are permitted.

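### Very vague main priors in the logistic models, combined with the 0.975/0.025 rule, give false-effect rates well above 5% for rare events such as SAEs

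*Protocol article*

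**What the plan says.** The Statistical analysis section of the protocol article fixes three things that bear on this point.

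- Model for the secondary objectives: "Bayesian linear regressions will be performed for continuous variables, and Bayesian logistic regressions for categorical variables".
- Priors: "The priors will be on the one hand very uninformative and on the other hand informative in the context of a sensitivity analysis". The vague prior therefore carries the main result, and the informative one is a sensitivity analysis.
- Decision rule: a factor counts as having an effect when "the probability that the effect is greater than the reference value is greater than 0.975 or less than 0.025". The same rule serves every analysis, and no exception is stated for sparse tables.

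Safety is a secondary objective (Aim and objectives), and the incidence of AEs and SAEs is a secondary outcome (Outcomes). Per patient this is a yes/no variable, so the logistic model would apply to it. Sample size determination sets 30 patients per arm. Safety considerations describes the intervention as low-risk and provides for no data monitoring committee.

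**The concern.** A wide normal prior on a log odds ratio is not neutral when one arm has no events. The likelihood then sets no lower bound on that arm's log odds, and only the prior stops the estimate from running towards minus infinity. The wider the prior, the more posterior mass lies on one side of zero, and the surer the analysis becomes about direction. A prior chosen to let the data speak ends up speaking for them.

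The thresholds 0.975 and 0.025 look like a two-sided 5% rule, and readers will take them that way. If they behave quite differently for rare events, the report could state that PRF prevents or causes a serious event on a handful of cases. With no data monitoring committee, the final analysis is where the article places its formal comparison of safety between arms.

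**Working it through.** **Inputs from the article.** 30 per arm, 1:1 allocation, logistic model, rule at 0.975/0.025.

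**Assumed inputs, because the article gives none.** Independent N(0, SD²) priors on the intercept *a* and the log odds ratio *b*, with SD 10, 31.6 (variance 1000) and 100. Equal true event rates in both arms: 3% and 5% as main cases, with 1%, 2% and 10% to show the range. Only the unadjusted model was computed.

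**The plan's own figure.** None is stated for the logistic analyses. The one computable figure concerns the VAS: 25 per group, difference 1, SD 1. Here 1/√(2/25) − 1.96 = 3.536 − 1.960 = 1.576, which gives 94.2% power; the noncentral t gives 93.4%, against 93.5% stated. Then 25 × 1.2 = 30 per arm, the figure used below. Posterior results with 25 per arm are almost the same.

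**Step 1, model.** logit p = a + b × arm. With no events in the PRF arm, its likelihood is (1 − p₁)³⁰, which tends to 1 as b → −∞. Only the prior limits b from below.

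**Step 2, posterior P(log OR > 0) by grid integration.**

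| Control vs PRF, of 30 | SD 10 | SD 31.6 | SD 100 |
|---|---|---|---|
| 1 vs 0 | 0.051 | **0.017** | **0.0055** |
| 0 vs 1 | 0.908 | 0.974 | **0.992** |
| 2 vs 0 | **0.015** | **0.005** | **0.0015** |
| 0 vs 2 | 0.9725 | **0.993** | **0.998** |

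Bold means that an effect is declared. For comparison, Fisher's exact p is 1.00 for 1 vs 0. For 2 vs 0 it is 2 × C(30,2)/C(60,2) = 2 × 435/1770 = 0.49. The single-event table crosses the threshold at SD of about 21.5 when the event is in the control arm and about 33 when it is in the PRF arm. A Metropolis run of 200,000 iterations with 10,000 burn-in agreed with the grid for the single-event tables (for example 0.052 and 0.909 at SD 10).

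**Step 3, false-effect rate.** Sum Bin(x₀; 30, π) × Bin(x₁; 30, π) over all tables that the rule declares.

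| True rate π in both arms | SD 10 | SD 31.6 | SD 100 |
|---|---|---|---|
| 1% | 3% | 22% | 39% |
| 2% | 8% | 31% | 50% |
| 3% | 12% | 33% | 48% |
| 5% | 14% | 27% | 34% |
| 10% | 8% | 10% | 10% |

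**Step 4, hand check at 3%.** P(0 events) = 0.97³⁰ = 0.401, P(1) = 30 × 0.03 × 0.97²⁹ = 0.372, P(2) = 435 × 0.03² × 0.97²⁸ = 0.167.

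- SD 100: every table with a zero in exactly one arm is declared, so 2 × 0.401 × 0.599 = 0.480.
- SD 31.6: 0 vs 1 drops out, so 0.480 − 0.401 × 0.372 = 0.331.
- SD 10: both single-event tables and 0 vs 2 drop out, so 0.480 − 2 × 0.149 − 0.401 × 0.167 = 0.115.

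These match the 3% row, so at this rate nearly all false effects come from zero cells.

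**Step 5, a weakly informative prior.** N(0, SD 2.5) on *b* with N(0, SD 10) on *a* gives 0.3%, 1.0%, 2.8% and 5.4% at true rates of 2%, 3%, 5% and 10%. With SD 2.5 on both parameters the rates at 3% and 5% are 2.5% and 4.5%, so the intercept prior matters and has to be stated too.

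**The case against.** The strongest reply is that the result hangs on a scale nobody can see here. The article condenses a fuller protocol; prior distributions and the handling of sparse tables are commonly left to that document or to the SAP, and their absence is no fault. That stands, and no missing scale is held against the article. What the article does fix is the direction: very vague priors carry the main result, and one rule applies throughout. Across the wide-prior range examined, that pairing exceeds 5% at event rates from 2% to 10%. The one exception in the table is SD 10 at a 1% rate (3%).

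A reader might infer that any single event will be declared an effect. The figures do not support that. At SD 10, already very wide for a log odds ratio, neither single-event table is declared. At SD 31.6 only the event-in-control direction is (0.017, against 0.974 for the reverse). Both directions need an SD above about 33.

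It is also fair that no AE or SAE rates are given, that the excess shrinks as events become common, and that a Bayesian rule need not promise a 5% error rate. The raw frequencies and the informative-prior analysis are already planned and could expose a conclusion driven by the prior. The article does not say, however, that either would override the main result.

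**Conclusion.** The concern holds for rare binary secondary outcomes, chiefly SAEs and individual AEs. Under the assumed normal priors and equal true rates of 3% and 5%, the stated rule declares a false effect in about 12% and 14% of trials at SD 10, 33% and 27% at SD 31.6, and 48% and 34% at SD 100. Even at SD 10, 2/30 in control against 0/30 with PRF is declared an effect although Fisher's p is 0.49. The prior scales and event rates are assumptions; the model, the choice of a vague main prior and the rule are the article's.

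Three extensions that a reader might draw are not supported:

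- **Analgesics.** The outcome is given only as "The use of analgesics", with no statement that it is categorical. The article also says "For residual postoperative pain, level 1, 2, or 3 analgesics are permitted", without distinguishing the arms. A near-empty table would arise only for a rarely used class.
- **Gene panel.** Expression is continuous, so the zero-cell mechanism does not apply. Multiplicity would be a separate question, and the article does not set out a family of between-arm gene comparisons on which to count it.
- **Primary outcome.** The VAS is analysed by linear or generalized regression, and nothing here affects it.

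This is worth changing before the analysis, but it is a matter for secondary outcomes only.

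**What to change.** In the analysis wording for logistic models:

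1. Make a weakly informative prior the main prior and state it for both parameters, for example N(0, SD 2.5) on the log odds ratio and N(0, SD 10) on the intercept.
2. Keep the very vague prior as a sensitivity analysis.
3. Report sparse AE and SAE categories as counts per arm with credible intervals for the risk difference (for example beta-binomial), and do not apply the 0.975/0.025 rule to them.

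The SD of 2.5 is one reasonable convention, not the only one. Whatever scale is chosen, its false-effect rate at low event counts can be checked in the same way. The cost is a change of wording and slight shrinkage of true secondary effects; no data collection or sample size changes.
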